### 2.11. Sample size considerations

The sample size was determined to be the minimum value, with which the lower limit of the 95% confidence interval (CI) (Clopper–Pearson method) of the binomial probability is lower than 0.10, when the point estimate of the probability is 0.875. The point estimate was presumed as it is the same with the probability of NHCAP cure with a 7 days administration of moxifloxacin in an existing report.^[15]^ Further, assuming that 0.30 of incorporated cases would be evaluated as “indeterminable,” the target case number was set to 77.

### 2.12. Statistical analysis

The target population in safety analyses (SAS) was defines as patients registered as study participants and administered the study drug at least once during the study period. The target population of the full analysis set (FAS) was defined as a subset of SAS consist of patients who are able to be evaluated whether “cured” or “not cured” at TOC. The modified FAS was defined as an extension of the FAS that includes patients who are able to be evaluated whether “cured” or “not cured” at the TOC or at the withdrawal from the protocol treatment. The target population in the per protocol set analysis was defined as patients with adherence of equal or higher than 80% to the protocol treatment (doses of the study drug).

The objective of the primary analysis is to obtain the lower limit of the 95% CI of the binomial probability of frequency of “cured.” The Clopper–Pearson method was planned to be used here. The FAS was planned as the target population.

A sensitivity analysis for the primary analysis is planned to evaluate the upward bias in the estimation of the probability of the treatment success, that will be introduced by the exclusion of cases who are withdrawn from the protocol treatment before TOC evaluation, obtained from the primary analysis. Aiming this, the modified FAS was set as the target population of the sensitivity analysis and the 95% CI of the binomial probability was planned to be calculated via the Clopper–Pearson method.

The planned analyses on the secondary endpoints are same with the primary analysis; the 95% CI of the binomial probability but the target population, that was set on the FAS.

Associations of the patients background and the primary/ secondary endpoints were planned to be analyzed exploratorily. The patients background was defined as the results from evaluations on respective patients at the visits for the first administration, or before the date, during the patient’s study period.

Planned subgroup analyses are the same procedure used in the primary analysis, after stratification of the patients with the following respective factors: risk of resistant bacteria (yes/no), aspiration risk assessed by standardized swallowing assessment (yes/no), and the first to the third most dominant bacterial species (presence/absence of bacteria with specific physiology, such as anaerobic bacteria, or types of bacteria) analyzed by a clone library method using amplified fragments of the 16S ribosomal RNA gene with universal primers in addition to conventional cultivation methods. The p-values obtained through the subgroup analyses will not be used to show the type I error rates for rejections of the respective null hypotheses.

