#### 2.8.3. Efficacy evaluation at the time of TOC.

TOC will be determined 5 to 10 days after the last dose of the study drug, with subjects classified as being cured, not cured, or indeterminable (lack of evaluation information, evaluation items worsening due to causes other than pneumonia, or clinical symptoms or inflammatory findings improved but the antibacterial drug was prescribed for reasons other than NHCAP before the time of TOC). Cured satisfies all the following criteria: treatment determined to be effective at the time of EOT; or an additional prescription of an antibacterial drug is not necessary after the EOT to the TOC; body temperature, WBC count, CRP level did not deteriorate after EOT, and resulting in an additional prescription of an antibacterial drug not being required; improved symptoms compared to the EOT; and improved chest X-ray compared to the EOT.

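### The sensitivity analysis for withdrawals accepts a cure rating that the endpoint definition does not support, so it captures the upward bias only in part

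*Protocol article*

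**What the plan says.** Three parts of the protocol article bear on this.

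- **Analysis sets (section 2.12).** The FAS, used for the primary analysis, is "a subset of SAS consist of patients who are able to be evaluated whether" cured or not cured at TOC. For the sensitivity analysis, "The modified FAS was defined as an extension of the FAS that includes patients who are able to be evaluated whether" cure was reached; that rating, in either direction, may be made "at the TOC or at the withdrawal from the protocol treatment". Its stated purpose is to evaluate the upward bias in the success probability that comes from leaving out patients who withdrew from protocol treatment before TOC. The method is again a 95% Clopper–Pearson interval.
- **Endpoint (section 2.8.3).** "TOC will be determined 5 to 10 days after the last dose of the study drug". Cure requires a list of criteria. They include no worsening of temperature, white cell count or CRP after EOT, no further antibacterial between EOT and TOC, and symptoms and chest X-ray both better than at EOT. Patients with missing information, with worsening from another cause, or given an antibacterial for another reason are indeterminable.
- **Sample size (section 2.11).** "the target case number was set to 77", "assuming that 0.30 of incorporated cases would be evaluated as" indeterminable.

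The article gives no rule for rating cure at withdrawal. It describes no analysis that includes patients who remain indeterminable. A per protocol set is defined but is not presented as a sensitivity analysis.

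**The concern.** The sensitivity analysis exists to show whether the primary cure rate is too favourable because withdrawn patients are missing from it. For that it needs an outcome for those patients that means the same as the primary outcome, or is deliberately stricter.

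The modified FAS offers neither. At withdrawal from treatment the patient is at EOT at best, so there is no later visit to set against EOT. Not cured can sensibly be assigned then; cured cannot, under the protocol's own definition. Yet the set is worded to accept both.

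Withdrawal is also likely to be related to outcome. Section 2.6 allows discontinuation for illness and adverse events, and the Discussion describes prompt changes of treatment after the Day 3 and Day 7 evaluations.

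At stake is how the main result is read. The primary objective of this single-arm study is the lower confidence limit of one proportion. If the modified FAS lands near the FAS, readers will take the result as robust to exclusions, when the agreement may come from ratings with no defined basis, and the patients who could not be rated at all are still absent.

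**Working it through.** **1. The plan's own figure.** Section 2.11 asks for the smallest n at which a condition on "the lower limit of the 95% confidence interval (CI) (Clopper–Pearson method) of the binomial probability" is met; the condition is worded as "is lower than 0.10, when the point estimate of the probability is 0.875". A lower limit that is itself below 0.10 gives no meaningful n, so I read 0.10 as the distance from 0.875 down to the limit. With a one-sided 95% limit and x = 0.875n, the smallest n is 54, and 54/(1 − 0.30) = 77.1, which matches 77 apart from rounding. (A two-sided limit would need n = 71 and 102 patients. That is a separate matter; here I need only the 54.)

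**2. Expected counts.**
- Evaluable at TOC: 77 × 0.70 = 53.9, taken as 54.
- Indeterminable: 77 − 54 = 23.
- Cured among the evaluable: 54 × 0.875 = 47.25, taken as 47.

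Intervals below are two-sided 95% Clopper–Pearson: lower limit Beta(0.025; x, n − x + 1), upper limit Beta(0.975; x + 1, n − x).

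**3. Primary analysis.** FAS: 47/54 = 0.870 (0.751–0.946).

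**4. Modified FAS.** If w of the 23 are rated at withdrawal and c of them are called cured, the estimate is (47 + c)/(54 + w). The article does not give w, so 5, 10 and 15 are assumptions.

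| Added (w) | None called cured | All called cured |
|---|---|---|
| 5 | 47/59 = 0.797 (0.672–0.890) | 52/59 = 0.881 (0.771–0.951) |
| 10 | 47/64 = 0.734 (0.609–0.837) | 57/64 = 0.891 (0.788–0.955) |
| 15 | 47/69 = 0.681 (0.558–0.788) | 62/69 = 0.899 (0.802–0.958) |

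The estimate exceeds the FAS value whenever c/w > 47/54 = 0.870. With 10 added, 9 called cured are enough: 56/64 = 0.875. Within each row the whole spread comes from a rating the article does not define.

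**5. All treated patients.** This assumes all 77 receive at least one dose.
- All 23 indeterminable counted as not cured: 47/77 = 0.610 (0.492–0.720).
- All 23 counted as cured: (47 + 23)/77 = 70/77 = 0.909 (0.822–0.963).

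From the FAS value there is 0.870 − 0.610 = 0.260 of room downwards and 0.909 − 0.870 = 0.039 upwards. The modified FAS reaches the lower bound only if all 23 are added and none is called cured.

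**6. The definitions side by side.** Section 2.8.3 says all criteria must be met. One item is joined by an 'or' that makes the list hard to read, but the symptom and chest X-ray comparisons with EOT stand as separate items. At a withdrawal visit that is itself the end of treatment, those items would compare the visit with itself.

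**The case against.** The strongest reply is that the two sections can be read together. Section 2.12 admits only patients who can be evaluated, and section 2.8.3 demands post-EOT data for cure. On that reading nobody without such data could be called cured, while an evident failure could be called not cured, which is conservative and close to the fix below. The reading is possible, but the text does not say so: it names both ratings at withdrawal and links neither to section 2.8.3.

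Four further points stand and limit the finding.

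- A reader might infer that the modified FAS leaves out every indeterminable patient. It does not: a withdrawn patient without a TOC rating enters if rated at withdrawal. Only those classifiable at neither time stay out.
- A reader might infer that the analysis cannot measure the bias at all. That goes too far. Its stated aim covers withdrawals only, and adding patients rated not cured captures part of that bias.
- A reader might infer that cures will be entered on an early impression while failures are omitted. Nothing in the article shows this will happen; the wording merely leaves room for it. Failures that force a change of treatment may be the easiest withdrawals to rate.
- The article condenses a full protocol, so the absence of an all-treated analysis here is not in itself a fault. The 0.30 is an allowance for indeterminable outcomes, not a withdrawal rate, and no success threshold is stated, so no decision flips.

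The conflict between what the article does fix remains: a rating at withdrawal against a cure definition tied to TOC.

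**Conclusion.** The point holds in limited form. The named sensitivity analysis addresses its stated target only in part, because it accepts a cure rating at a time when the protocol's own criteria cannot be met. Such ratings could mask the bias or push the estimate above the FAS value.

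The size of the effect depends on an unstated number of withdrawals, so the modified FAS figures are illustrations. The all-treated range of 0.610 to 0.909 rests only on the protocol's planning values (77 patients, 0.30 indeterminable, cure probability 0.875), rounding to whole patients, and all 77 being treated. It shows how much the remaining exclusions could matter, not what is expected. The change is worth making before the data are analysed; the primary analysis itself is not called into question here.

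**What to change.** 1. In the sensitivity analysis of section 2.12, do not accept cured at withdrawal. Count a patient withdrawn before TOC as not cured, unless an assessment 5 to 10 days after the last dose met the criteria of section 2.8.3.
2. Add a supportive analysis on the SAS with all remaining indeterminable patients counted as not cured and, for the range, as cured, each with its Clopper–Pearson interval.
3. Leave the primary FAS analysis unchanged.

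The cost is a change of wording and a few table rows. No new data, visits or patients are needed, and treatment is not affected. The price is a less favourable lower bound: patients who leave for reasons unrelated to pneumonia, such as withdrawn consent or a positive SARS-CoV-2 test, would count as not cured. That is conservative, so these rows should be labelled as bounds and not as estimates of the cure rate.

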#### 2.9.2. Secondary endpoints.

The secondary endpoints are as follows: Clinical efficacy at the time of EOT; Early clinical efficacy 3 days after the first administration; Microbiological efficacy at the time of TOC (each causative bacteria, each subject); Microbiological efficacy at the time of EOT (each causative bacteria, each subject).

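### Day 3 and end-of-treatment efficacy are analysed only in patients who can later be rated at test of cure, so valid early ratings are dropped and no sensitivity analysis covers the loss

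*Protocol article*

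**What the plan says.** Section 2.9.2 lists among the secondary endpoints "Clinical efficacy at the time of EOT" and "Early clinical efficacy 3 days after the first administration", together with microbiological efficacy at EOT and at TOC.

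Section 2.12 defines the FAS as a "subset of SAS consist of patients who are able to be evaluated whether “cured” or “not cured” at TOC". It gives the secondary endpoints the same analysis as the primary one: "the 95% CI of the binomial probability but the target population, that was set on the FAS".

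The same section says "A sensitivity analysis for the primary analysis is planned to evaluate the upward bias" in the success probability, and names as its source the "exclusion of cases who are withdrawn from the protocol treatment before TOC evaluation". For that purpose "the modified FAS was set as the target population of the sensitivity analysis". No corresponding analysis is stated for Day 3 or EOT.

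Section 2.8.3 gives three routes to an indeterminable TOC rating: missing evaluation information, worsening from a cause other than pneumonia, and improvement with an antibacterial given before TOC for something other than NHCAP.

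**The concern.** Day 3 and EOT ratings are made before TOC, yet a patient enters their denominators only if TOC later proves evaluable. For a patient who completes treatment, the last dose is on day 7 to day 10 and TOC follows 5 to 10 days later, that is, on day 12 to day 20. A Day 3 rating is therefore kept or discarded according to something that happens 9 to 17 days afterwards.

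At TOC, an evaluability restriction at least concerns patients whose outcome is unknown. At Day 3 and EOT it can discard outcomes that are known. The Discussion (section 3) describes a prompt change of treatment after the Day 3 and Day 7 assessments, so patients doing badly early are plausible candidates for leaving before TOC. The Discussion also wants the Day 3 result to be comparable with pneumonia results from overseas. A rate restricted to patients rated at TOC serves that aim poorly.

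The population sentence is also unclear in itself. It sets the secondary population apart from the primary one and then names the same set, the FAS. A reader cannot tell whether another set was meant.

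**Working it through.** **Who is dropped (section 2.12 against section 2.8.3)**

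| Patient | TOC rating | In FAS? | Effect of the restriction on Day 3/EOT rates |
|---|---|---|---|
| Early failure, antibacterial changed because pneumonia did not respond, followed to TOC | can be not cured | yes | none |
| Early failure, withdrawn, no TOC information | indeterminable | no | rate pushed up |
| Early responder, lost before TOC | indeterminable | no | rate pushed down |
| Improved, antibacterial given for a reason other than NHCAP | indeterminable | no | probably pushed down |

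**Planning figures (section 2.11)**

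The target is 77 cases with 0.30 assumed indeterminable. Then 77 × 0.70 = 53.9, so about 54 patients are in the FAS and 77 − 54 = 23 are outside it. In reverse, 54/0.70 = 77.1, which agrees with the stated 77.

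**Formula**

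Let *m* of the excluded patients have a valid early rating and *k* of these be failures. If the FAS shows 46/54 effective, the rate in everyone evaluable at that time point is

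(46 + *m* − *k*) / (54 + *m*).

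This is below 46/54 = 85.2% exactly when *k*/*m* exceeds the FAS failure share, 8/54 = 14.8%.

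The 46/54 and the values of *m* and *k* are assumptions, because the article gives none. All 54 FAS patients are taken to have an early rating.

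**Results**

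- Neutral case: *m* = 23, all responding at the FAS rate. 23 × 46/54 = 19.6 responders, and (46 + 19.6)/77 = 85.2%. There is no bias. In whole patients, 3 failures give 66/77 = 85.7% and 4 give 65/77 = 84.4%.
- Eight early failures, with the other 15 responding at the FAS rate: 15 × 46/54 = 12.8, taken as 13 responders. (46 + 13)/77 = 59/77 = 76.6%, a fall of 8.6 points. This implies 8 + 2 = 10 failures among the 23.
- Exactly eight failures, with the other 15 all responding: (46 + 15)/77 = 61/77 = 79.2%.
- Eight failures evaluable and the other 15 without an early rating (*m* = *k* = 8): 46/62 = 74.2%.
- Extremes with *m* = 23: all fail, 46/77 = 59.7%; all respond, 69/77 = 89.6%.

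**The case against.** The strongest reply has four parts.

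First, a reader might infer that every patient who fails early and changes treatment disappears from the Day 3 and EOT rates. The article does not support that. Under section 2.8.3, a change of antibacterial because the pneumonia did not respond is not a ground for an indeterminable rating. Such a patient can be rated not cured and stay in the FAS. This stands, and it confines the problem to patients without an evaluable TOC. It does not remove the problem, because section 2.12 itself says that withdrawals before TOC are excluded.

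Second, a reader might infer that conditioning on a later rating must inflate the early rates. It need not. Patients who improved but received an antibacterial for another reason are also excluded, and losing them lowers the rate. The article's own statement of upward bias concerns withdrawals and the primary cure rate. This stands too: upward is the probable direction, not a certain one.

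Third, the population sentence is garbled, and the FAS may be a slip. That is possible, but the FAS is what the text says, and the sentence needs correcting on either reading.

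Fourth, these are secondary endpoints in a single-arm study, reported as confidence intervals, and the primary result is unaffected. The article also does not say that these endpoints exist to capture early failure; the reason it gives for the Day 3 endpoint is comparability with overseas results. This limits the weight of the point but does not answer it.

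**Conclusion.** The point holds in limited form. As written, valid Day 3 and EOT ratings are left out of their own analyses when TOC is not evaluable, and no planned analysis shows the effect. The article recognises the corresponding bias for the primary endpoint and checks it there only.

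The size cannot be known from the article. On its planning figures about 23 of 77 patients are at issue. An illustrative 85.2% stays at about 85% if the excluded patients respond as the FAS does, and becomes 76.6% if 8 of them are early failures and the rest respond at the FAS rate. Both figures assume that all 23 have a valid early rating. That is generous, since missing information is one of the reasons for being indeterminable. The 76.6% shows what could happen and is not an expected value.

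This should be corrected, but it does not threaten the primary analysis.

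**What to change.** Rewrite the population sentence in section 2.12:

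1. Analyse Day 3 and EOT clinical efficacy, and EOT microbiological efficacy (which falls under the same sentence), in all SAS patients evaluable at that time point, whether or not TOC is evaluable.
2. For these analyses, count withdrawal or change of antibacterial for lack of effect before the assessment as no effect or ineffective. Such patients are then in the denominator.
3. Add a sensitivity analysis in the full SAS with indeterminable ratings counted as failures. This gives a lower bound and settles how the indeterminable categories of sections 2.8.1 and 2.8.2 enter it.
4. Remove the wording that contrasts the secondary population with the primary one, or name the different set that was intended.

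The cost is analysis wording and a few extra table rows. Day 3 and EOT assessments are already scheduled (section 2.6) and entered in the EDC system (section 2.10). Step 2 assumes that the reason for stopping or changing treatment is recorded there. The downside is that reported rates may be lower, by an amount that depends on how the excluded patients fared.

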## 3. Discussion

The efficacy and safety of LSFX for CAP have been shown in clinical trials. NHCAP is pneumonia with a higher risk of resistant bacteria and death compared to CAP. The described study will evaluate the efficacy and safety of LSFX for NHCAP.

LSFX is a quinolone antibiotic that exhibits antibacterial activity against a relatively wide range of bacterial species, including anaerobic bacteria, by inhibiting DNA gyrase and topoisomerase IV.^[3,4]^ Its efficacy and safety against respiratory and otorhinolaryngological infections have been shown in a phase III trial, and it received pharmaceutical approval in September 2019. While the existing quinolone antibiotics strongly inhibit either DNA gyrase or topoisomerase IV, LSFX inhibits both to a similar degree. Thus, it is anticipated to minimize resistant bacteria.^[3,5,6]^ Aspiration is common in NHCAP and pneumonia often recurs, thus, LSFX with a limited risk of resistant bacteria could be a useful option.

LSFX is an oral antibacterial drug and is intended for patients with NHCAP with mild-to-moderate symptoms that could be treated with oral formulations. Though injectable monotherapy is recommended for NHCAP with a risk of resistant bacteria, in actual clinical settings, NHCAP cases that can be treated in an outpatient setting are treated with respiratory quinolones. A risk of resistant bacteria is not necessarily a prognostic factor,^[4]^ and the described study uses a system that allows prompt change in treatment upon appropriately evaluating the condition on Day 3 and 7 of treatment. As such, if a principal investigator or subinvestigator determines it to be appropriate, patients with a risk of resistant bacteria are also allowed to participate.

Based on the evaluation method for NHCAP, according to respiratory infections in the guidelines related to the clinical evaluation methods for antibacterial drugs,^[15]^ the primary endpoint will be set as the TOC. This is the same as the efficacy evaluation for CAP. An early-stage efficacy evaluation will also be set for the secondary endpoints, but these are items recommended as primary endpoints in the Guidance Document for Community-Acquired Bacterial Pneumonia: Developing Drugs for Treatment published by the FDA.^[16,17]^ Thus, evaluation items that could be compared with pneumonia treatment results from overseas will also be included.

The study will evaluate the first to third most dominant bacterial species through exhaustive microbiome analysis (clone library method) of the tongue coating and sputum at the time of pneumonia diagnosis. Oral bacteria include many anaerobic bacteria and the detection of bacteria is extremely difficult in a normal culture test. However, the exhaustive microbiome analysis does not require culture, and exhaustively detects the 16s rRNA gene; thus, it is an especially useful detection method for bacterial species when culturing is difficult.^[18]^ Since many cases of NHCAP are aspiration pneumonia, we assume that by comparing the microbiome in the tongue coating and sputum, the relationship between NHCAP and oral bacteria can be evaluated.

In the study, the efficacy and safety of LSFX against NHCAP, will be presented with the hope of increasing the therapeutic options for NHCAP. The study will be a significant contribution in establishing an appropriate therapeutic system.
